#### 7.2.5.6 Satisfaction questionnaires

Satisfaction at Day 7 will be compared between groups using ANCOVA and will include covariates for outcomes measured at baseline as well as site, age, sex, ethnicity, race, treatment seeking, and insurance status (see **Exhibit 2**). Linear contrasts will be used to estimate treatment differences along with 95% confidence intervals in XR vs. SL.

#### **7.2.5.7 Overdose events**

A summary table will be provided with the number of non-fatal opioid overdoses by treatment and visit (baseline and Day 30 follow-up). At the baseline visit, participants are asked about overdoses in the past 30 days. The number of ODs where NARCAN (naloxone) was used to reverse overdose, that resulted in treatment at an ED, and that resulted in being admitted to the hospital will also be summarized (among the 5 most serious opioid overdoses reported by the participant at each visit). The number of participants with at least one opioid overdose and the number of opioid overdoses per participant (including participants experiencing no opioid overdoses) will also be summarized.

Counts of overdose events in the 30 days from randomization will be compared between groups using negative binomial regression. These models will include covariates for outcomes measured at baseline as well as site, age, sex, ethnicity, race, treatment seeking, fentanyl in UDS, and insurance status (see **Exhibit 2**). Linear contrasts will be used to estimate treatment differences along with 95% confidence intervals in XR vs. SL.

#### **7.2.6 Exploratory Outcomes**

A set of patient and ED characteristics will be evaluated for their potential effect on the effectiveness outcomes. These characteristics will include items such as type of opioid used (fentanyl vs. heroin vs. prescription), frequency, and mode of use (IV/nasal); demographics; pain intensity and interference; reason for ED presentation such as OD, specifically seeking treatment for OUD, or reason related to substance use, presence of depressive symptoms, prior receipt of MOUD, comorbid substance use, recent homelessness, referral to office-based versus opioid treatment programs, results of the Treatment Effectiveness Assessment, whether naloxone dispensed or prescribed at discharge as well as logistical issues that prevented engagement in treatment such as transportation, court dates etc.

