| Treatment Effectiveness Assessment                       | 1'   | RA      |                                                                                                        |                                                                             | X                   | X                    |
| Injection Site Assessment for XR-BUP                     | 1'   | RA      |                                                                                                        |                                                                             | X                   | X                    |
| Healthcare Visit Logistics                               | 1'   | RA      |                                                                                                        |                                                                             | X                   | X                    |
| Engagement in Treatment                                  | 5'   | RA      |                                                                                                        |                                                                             | X                   | X                    |
| Total Duration in Minutes for Follow-Up                  |      |         |                                                                                                        |                                                                             | 40'                 | 35'                  |
| RA/PI Assessments                                        |      |         |                                                                                                        |                                                                             |                     |                      |
| ED Visit Review                                          |      | RA      |                                                                                                        |                                                                             | X                   |                      |
| ED Visits and Hospitalizations (EHR)                     |      | RA      |                                                                                                        |                                                                             |                     | X                    |

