### 8.7.9 Health Status

The Health Status form collects information on HIV and Hepatitis C status, HIV risk (CTN HRBS), Pain (PEG), and psychological health (PHQ-9) usual care and reason for ED visit. The HIV

Risk-taking Behaviour Scale (HRBS) is a brief, 12-item questionnaire measuring the behavior of people who inject drugs that puts them at risk of either contracting/transmitting HIV. Also embedded within is the Patient Health Questionnaire (PHQ-9) used to assess depressive symptoms including suicidal ideation. For in-person research visits in the ED, if the participant responds to “Thoughts that you would be better off dead, or of hurting yourself in some way” with any response other than “Not at all,” it will prompt the RA to notify the attending physician and will trigger the completion of the Mental Health Assessment (MHA) form by the RA. For participant visits not conducted in person, if the participant responds to “Thoughts that you would be better off dead, or of hurting yourself in some way” with any response other than “Not at all,” the RA will provide national and/or local mental health resource referral/contact information to the participant and it will trigger the completion of the Mental Health Assessment (MHA) form by the RA. All sites should monitor participant responses to this question or if a participant spontaneously expresses potential suicidal/homicidal ideation and have procedures in place to ensure patient safety.

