#### 8.7.17 Treatment Effectiveness Assessment

This form collects self-report data across four domains: substance use, health, lifestyle, and community and is collected at 7 days and at 30 days post study enrollment.

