#### 8.7.19 Healthcare Visit Logistics

The Healthcare Visit Logistics form asks cost data questions at 7 days and 30 days post study enrollment as well as barriers to care, i.e., transportation, filling the prescription or lack of identification.

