### **8.8.2 ED Visit Review Implementation/Process Outcome**

The ED Visit Review (EDR) form collects information about study and clinical processes surrounding the index ED visit. It is completed by the RA by performing a medical record abstraction. On an ongoing basis, the site's RA fills out one form for each participant.

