### 7.2.3 Supportive Analyses of the Primary Outcome Measure

The primary outcome will be analyzed as above for the PP population.

Given the relative advantages of Generalized Estimating Equations and generalized linear mixed models (GLMM), sensitivity analyses will compare treatments using a logistic regression with SAS PROC GLMMIX, with a random effect for subject.

```
proc glimmix data = primdat;
  class engage site site2 (ref = '02156') patid trt (ref = 'SL-BUP')
    visno (ref = 'C07') gender (ref = '1') race_cat (ref = '1')
    ethnic_cat (ref = '0') insurance_rand (ref = '1');
  model engage (event = '1') = trt visno trt * visno site2 age gender
    race_cat ethnic_cat insurance_rand /*prior_engagement*/ /
    dist = bin link = logit;
  random _residual_ / subject = patid type = cs;
  weight wgt;
  lsmeans trt * visno / pdiff oddsratio cl;
run;
```

Additional sensitivity analyses may be conducted to evaluate the effect of changes in eligibility criteria.

The supportive analyses of the primary outcome will be analyzed for the ITT and PP populations.

Subgroup analyses for sex, race, ethnicity, and age will be performed as required by the NIH (NIH, 2016). The proportions and confidence intervals for each of the primary outcome measures will be estimated in the following subgroups for the ITT population:

- 1) Males and females

- 2) Black, White, and all other races
- 3) Hispanic and non-Hispanic participants
- 4) Participants older than the median age and those equal to or younger than the median age.

The primary analysis will be re-run with a covariate for the subgroup and the interaction between the subgroup and treatment. Estimate statements will be used to determine the treatment effects and associated confidence intervals for each group.

Additional subgroups of interest include the following:

- 1) Housing status at baseline (unstable housing in last 12 months (DM1.DMNIGHT = yes versus no); currently in unstable housing (DM1.DMLIVING = yes versus no))
- 2) Fentanyl positive (UDS.UDFEN1 = positive) and fentanyl negative (UDS.UDFEN1 = negative) from baseline UDS
- 3) Stimulant positive (UDS.UDAMP1 = positive or UDS.UDMET1 = positive) and stimulant negative (UDS.UDAMP1 = positive and UDS.UDMET1 = positive) from baseline UDS
- 4) Treatment seeking at the index ED visit (EDR.ERPRBTYP = 'Seeking referral for OUD treatment' versus other reasons)
- 5) Overdose at the index ED visit (EDR.ERPRBTYP = 'Overdose' versus other reasons)

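### SAP 7.2.6 treats two items recorded only at or after Day 7 (the Treatment Effectiveness Assessment and barriers to engagement) as possible influences on engagement, so their association with Day 7 engagement is partly or wholly circular

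*Combined protocol and SAP*

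**What the plan says.** SAP 7.2.6 opens: "A set of patient and ED characteristics will be evaluated for their potential effect on the effectiveness outcomes". Most of its list describes the patient or the ED at presentation, such as type of opioid, demographics and reason for the visit. It closes with "results of the Treatment Effectiveness Assessment, whether naloxone dispensed or prescribed at discharge as well as logistical issues that prevented engagement in treatment". Protocol 8.2.2 carries the same list, so this is not a slip in the SAP. Neither section gives a time point or a model, and neither separates items known before randomisation from later ones.

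The timing is set elsewhere in the protocol:

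- The Treatment Effectiveness Assessment "is collected at 7 days and at 30 days post study enrollment" (8.7.17). Table 2 agrees and shows nothing at screening or enrollment.
- The Healthcare Visit Logistics form "asks cost data questions at 7 days and 30 days post study enrollment as well as barriers to care" (8.7.19). Table 2 again shows Day 7 and Day 30 only.
- The Engagement in Treatment survey, which supplies the participant's report for the primary outcome, is in the same two columns of Table 2. SAP 7.2.1 defines the primary outcome at Day 7.

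A related point concerns the source of two subgroup factors. SAP 7.2.3 defines "Treatment seeking at the index ED visit (EDR.ERPRBTYP = 'Seeking referral for OUD treatment' versus other reasons" and takes overdose presentation from the same variable. Of the form involved, protocol 8.8.2 says: "It is completed by the RA by performing a medical record abstraction". Table 2 places "ED Visit Review" in the 7-Day column, and SAP 2.2.5.2 states that the trial is unmasked. The Health Status form, which Table 2 schedules at enrollment and at both follow-ups, also covers "usual care and reason for ED visit" (protocol 8.7.9).

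**The concern.** A predictor is informative about an outcome when it is settled first. Here two of the listed items are obtained in the same telephone interview as the outcome they are meant to explain. Someone who has not reached treatment by Day 7 is likely to be asked, or to volunteer, what stood in the way. Someone who has reached it has less reason to recall a transport or prescription problem. The SAP's wording of the barrier item strengthens this, because it describes issues by their having stopped engagement. The Treatment Effectiveness Assessment is a self-rating of substance use, health, lifestyle and community, and being in treatment can itself move that rating.

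Two consequences follow. First, a table of factors affecting engagement would show strong associations for these items that say little about cause. That could misdirect implementation work, because logistical barriers are the trial's stated rationale for XR-BUP. Second, if either item entered a model with treatment arm, it would be a post-randomisation variable that the treatment may itself affect, and the arm coefficient would no longer be the randomised comparison.

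**Working it through.** The plan attaches no number to this analysis. The only design figure needed is the engagement odds ratio implied by SAP 10.2 (45% SL-BUP, 53% XR-BUP): (0.53 × 0.55)/(0.45 × 0.47) = 0.2915/0.2115 = 1.38. Everything below that goes beyond this figure rests on assumed inputs and shows a mechanism; none of it is a forecast.

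**1. Order of events.** Randomisation is Day 0. Both items and the participant's report of engagement are first taken at the Day 7 contact. SAP 3.2.2.3 allows that contact to take place later than Day 7, so answers may be given with hindsight. For Day 30 outcomes, a Day 7 value does come earlier, but it is still post-randomisation.

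**2. A barrier with no real effect.** Assume true prevalence b, unrelated to engagement. Affected non-engaged patients report it with probability 0.9, and affected engaged patients with probability r. Then

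false OR = [br/(1 − br)] / [0.9b/(1 − 0.9b)].

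- r = 0.9: the OR is 1.00 for any b.
- r = 0.6: b = 0.2 gives (0.12/0.88)/(0.18/0.82) = 0.62; b = 0.4 gives (0.24/0.76)/(0.36/0.64) = 0.56.
- r = 0.3: 0.29 and 0.24.
- r = 0.1: 0.09 and 0.07.

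The whole association comes from differential reporting.

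**3. The Treatment Effectiveness Assessment in a model with arm.** Assume the Day 7 score is normal with SD 1 within each arm-by-engagement group, a higher in engaged patients and d higher with XR-BUP. By Bayes' rule, the arm coefficient in a logistic model that includes the score is

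adjusted log OR = ln(1.38) − a × d = 0.321 − a × d.

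- a = 0.5, d = 0.2: 0.321 − 0.10 = 0.221, OR 1.25.
- a = 1.0, d = 0.2: 0.321 − 0.20 = 0.121, OR 1.13.
- d = 0: OR stays at 1.38.

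So absorption needs XR-BUP to move the score by a route other than engagement. That is plausible for a rating that covers substance use, but it is not established.

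**4. The primary analysis.** The text and code in SAP 7.2.2 adjust for site, age, sex, race, ethnicity, insurance and prior engagement. Neither item appears in the outcome model or in the dropout models.

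**5. Treatment seeking from the chart review.** Let s be the true share of seekers, unrelated to engagement. Suppose a fraction m of engaged non-seekers is coded as seekers in the XR arm only. The false ratio of odds ratios (seekers to non-seekers) is [1 + m(1 − s)/s]/(1 − m). With m = 0.10 this is 1.10/0.90 = 1.22 at s = 0.5, and 1.233/0.90 = 1.37 at s = 0.3. If the same m applies in both arms, the factor cancels and the ratio is 1.00. A false subgroup effect therefore needs miscoding that differs by arm.

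**The case against.** The case against has real force on several points.

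- SAP 7.2.6 is exploratory, is assigned to the Lead Node in Exhibit 1, and belongs to RCT sections that Exhibit 5 calls a first draft, to be finalised in version 4.0. It never calls its list baseline and names no model. All of this stands. It limits the weight of the point but does not remove the circularity, and it means the repair can still be made in time.
- A reader might infer that engagement among people with a barrier is zero by construction. The SAP's phrase invites that, but protocol 8.7.19 describes a form about barriers to care in general, and Table 2 does not restrict it to people who failed to engage. An engaged participant can report a transport problem. Differential reporting is plausible; a structural zero is not shown.
- A reader might infer that the treatment estimate is biased. The primary model contains neither item, and no passage places either in a model with arm. The adjusted odds ratios in the working show what could happen if someone did so.
- A reader might infer that the treatment-seeking and overdose subgroups, or the secondary models in SAP 7.2.5.4 to 7.2.5.7 that adjust for treatment seeking, are contaminated by the outcome. The documents do not support that. The ED Visit Review abstracts a fact about the index visit from the chart, and protocol 8.8.2 describes completion as ongoing. No passage says it is coded after engagement is known, and nothing documents miscoding that differs by arm. What remains is an opportunity for it: unmasked staff and a Day 7 slot in Table 2.

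**Conclusion.** The point holds for the Treatment Effectiveness Assessment and for logistical barriers. Both are collected only at Day 7 and Day 30, at the same contact as the participant's report of the outcome, yet SAP 7.2.6 examines them as influences on it. Their association with Day 7 engagement cannot be interpreted as an effect. How far it misleads depends on reporting behaviour that the documents do not describe: in the illustration, from no distortion with equal reporting to an odds ratio of 0.07 for a barrier that does nothing. Any loss of treatment effect through adjustment is conditional on a model that the SAP does not state, and on XR-BUP shifting the rating independently of engagement.

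The consequence is confined to the exploratory analyses. The primary weighted GEE and the sample size are untouched. For treatment seeking and overdose presentation the documents support a precaution, not a finding of bias. The change is worth making because it is specific and nearly free, and because the SAP is still open.

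**What to change.** In SAP 7.2.6, limit predictors and effect modifiers to variables fixed before randomisation. For items measured repeatedly, such as pain and depressive symptoms on the Health Status form, name the enrollment value. Report the Treatment Effectiveness Assessment and the logistical barriers descriptively by arm, as post-randomisation outcomes.

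The cost is SAP wording and the loss of two exploratory predictors; no data are lost. Referral type and naloxone at discharge are also settled during or after the index visit's treatment. They precede the Day 7 outcome and are not circular in the same way, but the revised text should say on which side of the line they fall.

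As a secondary precaution only, compare treatment seeking and overdose presentation from the ED Visit Review with the reason for ED visit on the enrollment Health Status form, and repeat the two subgroup analyses with that source as a sensitivity check. This is possible only if the form separates these categories. The documents do not show its response options, it may be coarser than the chart, and no passage states that it is completed before randomisation. It should therefore not replace the chart source by default.

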#### **7.2.7 Missing Data**

Several strategies were imposed to accommodate the likelihood that missing data will occur during this study including prevention, strict data collection procedures, careful selection of variables without large proportions of missing values, and regular monitoring of the trial. Despite these prevention efforts it is reasonable to assume missing data will occur. Our proposed primary and secondary analyses make use of all available data and are valid under the assumption that missing data will be missing at random (MAR) (Diggle, et al., Molenberghs, et al.). We may evaluate the plausibility of this assumption by determining the extent of missing data and use logistic regression to identify factors associated with missing data. We may conduct sensitivity analysis using a pattern-mixture approach implemented using multiple imputation under missing not at random (MNAR) assumptions to examine the robustness of conclusions of the primary analysis to missing data (Little, et al., Molenberghs, et al.).

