#### 12.6.3.2 Analysis of Primary Effectiveness Outcome

The primary outcome, treatment engagement at 7 days (Y/N), will be assessed for all randomized patients that are enrolled in the study. Treatment engagement will also be assessed at 30 days. Intervention differences (XR vs. SL) for this dichotomous outcome will be examined using weighted GEE. The traditional GEE approach is valid under the strong assumption that missing data is missing completely at random (MCAR). Robins, Rotnitzky and Zhao proposed an extension of GEE called the weighted GEE to alleviate this restrictive assumption. The weighted GEE provides consistent parameter estimates when the dropout mechanism is correctly classified by implementing the inverse-probability weighted method to account for dropouts under the missing at random (MAR) assumption. Inverse probability weights are estimated by a logistic regression of dropout at a particular measurement occasion. Our dropout model will include baseline demographic and clinical characteristics including treatment engagement prior to enrollment, site, intervention group, insurance status and time as well as outcomes at previous timepoints. From the dropout model, predicted probabilities of dropout will be estimated for each subject at each post-randomization timepoint. The predicted probabilities will then be translated into weights where the weight is the inverse of the cumulative probability of dropping out at a particular assessment. The weighted GEE model will contain an effect for intervention (XR vs. SL). An exchangeable working correlation will be used to account for clustering of responses from the same participants (i.e. 7 and 30 days). The model will also include treatment engagement in prior 12 months at baseline, age, sex, ethnicity/race, insurance status and site. Linear contrasts will be used to estimate odds ratios, treatment differences and 95% confidence intervals for the proportions of participants that engage in treatment in XR vs. SL at both 7- and 30-days follow-up. Given the relative advantages of Generalized Estimating Equations and generalized linear mixed models (GLMM) sensitivity analyses will compare treatments using a logistic regression with GLMM, with a random effects for subject. Additional sensitivity analyses may be conducted to evaluate the effect of changes in eligibility criteria.

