### 12.6.3.3 Analysis of Secondary Effectiveness Outcomes

Craving and satisfaction assessed at 7 days will be compared between groups using ANCOVA. Counts of self-reported opioid use, health service utilization and overdose events will be compared between groups at both 7 and 30 days using negative binomial regression. All of these

models will include covariates for outcomes measured at baseline as well as site, age, sex, ethnicity/race, treatment seeking and insurance status. Linear contrasts will be used to estimate treatment differences along with 95% confidence intervals in XR vs. SL.

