## 12.6.7 Plan for Missing Data

Several strategies will be imposed to accommodate the likelihood that missing data will occur during this study. Prevention is the most obvious and effective manner to control bias and loss of

power from missing data. Prior to the trial we will establish data collection procedures. Variables with large proportions of missing will be excluded from collection. We will follow the intent to treat principle, requiring follow-up of all participants randomized regardless of the treatment received. Regular data entry into case report forms (CRFs) and data retrieval from EHRs combined with monitoring and missing data reports will trigger protocols for tracking and obtaining missing data. Despite these prevention efforts it is reasonable to assume missing data will occur. Our proposed primary and secondary analyses make use of all available data and are valid under the assumption that missing data will be missing at random (MAR). We may evaluate the plausibility of this assumption by determining the extent of missing data and use logistic regression to identify factors associated with missing data. We may conduct sensitivity analysis using a pattern-mixture approach implemented using multiple imputation under missing not at random (MNAR) assumptions to examine the robustness of conclusions of the primary analysis to missing data.

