#### 7.2.4 Definition of Secondary Outcome Measures

The secondary outcomes are defined below and will be analyzed for the ITT population only.

The following are considered the key secondary outcomes and will be analyzed by the DSC:

1. Engagement in MOUD at 7 days
2. Engagement in formal addiction treatment at the 30 days
3. Engagement in MOUD at the 30 days
4. Self-reported days of illicit opioid use (past 7 days) measured by TLFB methods at 7 days
5. Self-reported days of illicit opioid use (past 7 days) measured by TLFB methods at 30 days

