#### **7.2.5.4 Self-reported days of illicit opioid use**

Counts of self-reported illicit opioid use will be compared between treatment groups at both 7 and 30 days using negative binomial regression. These models will include treatment and covariates for outcomes measured at baseline as well as site, age, sex, ethnicity, race, treatment seeking, and insurance status (see **Exhibit 2**). Linear contrasts will be used to estimate treatment differences along with 95% confidence intervals for XR vs. SL at each follow-up time.

| Exhibit 2: Covariates for Primary and Secondary Outcomes |                        |                           |                                                                  |
|-----------------------------------------------------------------|------------------------|---------------------------|------------------------------------------------------------------|
| Covariate                                                | Variable name   | Coding in analysis | Comments                                                  |
| Treatment                                                       | COREVARS.TRT           | categorical               | XR-BUP, SL-BUP                                                   |
| Visit                                                           | VISNO                  | categorical               | Day 7, Day 30                                                    |
| Site                                                            | DEM.SITE               | categorical               |                                                                  |
| Age                                                             | DEM.DEBRTHDT           | continuous                | Age at randomization                                             |
| Sex                                                             | DEM.DESEX              | categorical               | Male, Female                                                     |
| Ethnicity                                                       | DEM.DEHISPNC           | categorical               | Hispanic, Non-Hispanic, Unknown/not reported                     |
| Race                                                            | DEM.WHITE, DEM.DEBLACK | categorical               | Black, White, Other, Unknown/not reported                        |

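### The plan claims missing-at-random validity for every secondary analysis, but nothing specified for Day 30 opioid-use days secures it

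*Combined protocol and SAP*

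**What the plan says.** **The general claim.** SAP 7.2.7: "Our proposed primary and secondary analyses make use of all available data and are valid under the assumption that missing data will be missing". The assumption it goes on to name is missing at random. Protocol 12.6.7 makes the same claim, that the analyses are "valid under the assumption that missing data will be missing at random (MAR").

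**Engagement and MOUD outcomes.** Protocol 12.6.3.2 explains why a device is needed: "The traditional GEE approach is valid under the strong assumption that missing data is missing completely at random (MCAR"). It therefore adds inverse-probability weights from a dropout model that includes outcomes at earlier visits. The code in SAP 7.2.2 puts Day 7 engagement into the Day 30 weight model. SAP 7.2.5.1 to 7.2.5.3 refer the three engagement and MOUD secondary outcomes back to that method.

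**Opioid-use days.** SAP 7.2.4 lists as a key secondary outcome: "Self-reported days of illicit opioid use (past 7 days) measured by TLFB methods at 30 days". SAP 7.2.5.4 states: "Counts of self-reported illicit opioid use will be compared between treatment groups at both 7 and 30 days using negative binomial regression". On covariates: "These models will include treatment and covariates for outcomes measured at baseline as well as site, age, sex, ethnicity, race, treatment seeking, and insurance status". Contrasts are for "XR vs. SL at each follow-up time". Protocol 12.6.3.3 has the same model: "Counts of self-reported opioid use, health service utilization and overdose events will be compared between groups at both 7 and 30 days using negative binomial". Neither section mentions weights, a random effect, a repeated-measures structure or a Day 7 term, and neither refers back to SAP 7.2.2.

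**The concern.** Missing at random lets the chance of a missing Day 30 value depend on anything observed, including Day 7 data. A Day 30 model that conditions only on treatment and baseline covariates is protected against a narrower set of mechanisms, namely those driven by its own covariates. The plan recognises this gap for engagement and closes it with weights. For opioid-use days it makes the same claim and specifies nothing that would support it.

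At stake is the XR-BUP versus SL-BUP difference on a key secondary outcome. If Day 7 use predicts being reached at Day 30, and does so differently in the two arms of this open-label trial, the comparison shifts while the SAP describes it as valid under missing at random. The only not-missing-at-random sensitivity analysis is optional and concerns the primary analysis.

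**Working it through.** **1. The plan's own figures reproduce.** SAP 10.2 gives 90% power for d = 0.16 with 850 per arm. Power = Φ(0.16 × √(850/2) − 1.96) = Φ(3.30 − 1.96) = 0.910. The exact requirement is 2 × (1.960 + 1.282)² / 0.16² = 821 per arm. For dropout, 850 / 0.85 = 1,000 per arm, or 2,000 in total. Sample size is not in question.

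**2. What the specified model needs.** Let R be the indicator that Day 30 use is observed, X the model's covariates including arm, and Y7 Day 7 use. A regression of Day 30 use on X among those observed is consistent if R is independent of Day 30 use given X. Missing at random grants only independence given (X, Y7). The two differ when Y7 predicts both R and Day 30 use.

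**3. Size by simulation.** From the documents: 15% missing, 1:1 allocation, counts of 0 to 7 days. Assumed: 30% missing as a second level; Day 7 to Day 30 correlation 0.32 to 0.54; one baseline covariate, adjusted for; Day 7 use always observed; log-odds of a missing Day 30 value linear in Day 7 days. There were 400,000 participants per scenario. Entries are Day 30 rate ratios, XR to SL.

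| Dependence of missingness on Day 7 use | Missing | Full data | Observed only | Weighted |
|---|---|---|---|---|
| None (covariates only) | 15% | 0.885 | 0.886 | 0.886 |
| Same in both arms, no effect | 15% | 0.999 | 0.999 | 0.999 |
| Same in both arms, XR lowers Day 7 use only | 15% | 1.000 | 1.003 | 0.997 |
| Same in both arms, XR lowers Day 7 use only | 30% | 1.004 | 1.015 | 1.004 |
| SL +0.2 per day, XR 0 | 15% | 0.999 | 1.021 | 0.997 |
| SL +0.3 per day, XR 0 | 15% | 1.000 | 1.037 | 1.000 |
| SL +0.2 per day, XR −0.2 | 15% | 1.000 | 1.040 | 0.999 |
| SL +0.2 per day, XR 0 | 30% | 0.999 | 1.050 | 1.001 |
| SL +0.2 per day, XR −0.2 | 30% | 1.002 | 1.087 | 1.002 |

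The weights used Day 7 use, arm and their interaction. In the arm-varying rows at 15%, the spurious difference is about 0.08 days (from −0.005 to 0.075) to 0.14 days (from 0.005 to 0.140).

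**4. Stacking both visits does not help by itself.** A two-visit negative binomial with visit and treatment-by-visit, but no weights or random effect, gave 1.039 where the Day 30 model gave 1.040 (15%), and 1.086 where it gave 1.087 (30%).

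**5. Effect of baseline adjustment.** On a standardised scale with d = 0.16, assume a Day 7 to Day 30 correlation of 0.4 to 0.6, odds of loss multiplied by 1.5 to 2 per SD of Day 7 use, and loss of 18% versus 12% or 20% versus 10%. The unadjusted bias is 6 to 24% of the effect. That is about 0.01 to 0.04 SD, or 0.2 to 0.8 standard errors (SE = √(2/850) = 0.049). Adjusting for a baseline value correlated 0.5 with both visits reduces it to about 2 to 14%. With equal loss it is about 0 either way.

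**The case against.** **The documents do not call this model unweighted or restricted to responders.** That is correct. A reader might infer that the plan prescribes a complete-case analysis that discards Day 7 data. The text supports only that no weighting or use of Day 7 data is specified.

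**Exhibit 2 lists Visit, so a joint model may be intended.** It may. Protocol 12.6.2.2 uses a negative binomial mixed model for the implementation counts, and a correctly specified mixed model would be valid under missing at random. None is specified for this outcome, and a plain stacked model leaves the bias unchanged.

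**SAP 7.2.4.4 imputes unknown days both as use and as no use.** It does not say whether a wholly missed visit counts as seven unknown days. If it does, nobody is dropped. Even so, imputing all use or no use is not a missing-at-random analysis, and it conflicts with protocol 12.6.1, which rules out imputation in secondary analyses.

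**The harm is assumed.** This largely stands. The documents give only about 15% loss overall, and a common mechanism produces almost no bias. A reader might also infer that participants who relapse are lost and so flatter one arm. The documents give no such pattern. Relapse after Day 7 is unobserved, so loss that depends on it would not be missing at random, and the weights proposed here would not correct it.

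**The SAP is unfinished.** Its revision history describes the RCT section as a draft to be finalised before database lock. That makes the change easy, but it does not make the sentence in SAP 7.2.7 correct.

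**Conclusion.** The concern holds in a limited form. The missing-at-random claim is broader than what is specified for opioid-use days. As written, the Day 30 comparison is secure only when missingness depends on the model's own covariates.

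It does not follow that the Day 30 result will be biased, and the point does not extend to the engagement and MOUD outcomes, which are weighted. Bias is nil or small under a common dropout mechanism. It is modest when dependence on Day 7 use differs by arm: rate ratios of about 1.02 to 1.04 under a true null at 15% missing, and 1.05 to 1.09 at an assumed 30%. These sizes rest on assumed correlations and loss patterns. The rate-ratio simulation adjusted for one baseline covariate, and a stronger baseline predictor would shrink them. The plan should be corrected on this point because it concerns a key secondary outcome and the change is small.

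**What to change.** - **SAP 7.2.5.4.** Fit the negative binomial model to Day 7 and Day 30 together, with treatment, visit, treatment-by-visit and the listed covariates, and standard errors clustered by participant. Weight each record by the inverse of the probability that TLFB is available at that visit. The dropout model includes treatment, baseline use and, for Day 30, Day 7 use and its interaction with treatment.
- **Participants missing Day 7.** Estimate their Day 30 observation probability from a separate baseline-only model. Otherwise a Day 30 weight model with Day 7 use as a plain covariate, as in the SAP 7.2.2 code for engagement, would drop them.
- **SAP 7.2.4.4.** State that the two-way imputation applies to unknown days within a completed TLFB and not to a wholly missed visit, and reconcile it with protocol 12.6.1.
- **SAP 7.2.7 and protocol 12.6.7.** Limit the missing-at-random sentence to the analyses that meet it.

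The cost is slightly wider confidence intervals and a little more programming. Sample size and power figures do not change.
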